Postnatally, infants are treated according to a standardised protocol for patients with CDH, which is implemented in all participating centres. This protocol was developed with the available evidence and consensus between the participating centres and was updated in June 2016.^10 16^ If the patient is diagnosed with PH in the first week of life, the patient will be allocated to one of the two study drugs (figure 1). iNO is provided by a tank connected to a ventilator. Different devices are used in different centres. Some centres use integrated systems, making it impossible to disconnect the iNO tank and replace it with another gas to facilitate a blinded intervention. Therefore, the study is open label. iNO is given with a starting dose of 20 ppm, which is the maximum dose.^18 19^ Sildenafil is given intravenously, using a loading dose of 0.4 mg/kg in 3 hours, followed by continuous infusion of 1.6 mg/kg/day.^20 21^ To wean the study drugs a standard protocol is followed (figure 2). The allocated drugs will be restarted as per protocol if criteria for its use are met again before the age of 14 days. To further standardise care, an inotropic support flow chart is included in the study protocol (figure 3). After day 14 treatment of PH will be at the discretion of the local medical team and the study drug can be changed to, for instance, sildenafil orally. The use of bosentan, milrinone and prostin next to the study treatment is allowed. The use of bosentan as add on therapy is allowed and is considered as PH treatment on day 14. The intervention will be prematurely stopped when the patient meets one or more of the defined failure criteria, described in point three of the secondary outcomes. Further treatment will then be at the discretion of the medical team and will be according to the standardised protocol.^16^ iNO and sildenafil can both be given outside the study protocol. An ECMO procedure may then be started in centres where ECMO is available. Data of all patients are used in the intention-to-treat analysis.

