### Data analysis

The patients will be analysed according to the group they are randomised to (intention-to-treat analysis). A p-value (two-sided) <0.05 is considered significant in all analyses. The primary endpoint will be analysed using multiple logistic regression with randomisation arm, centre, observed/expected head-lung ratio, position of the liver, side of the defect, defect size and ventilation modality as independent variables.^25^ If necessary, multiple imputation using the fully conditional specification method will be used to account for missing data in the independent variables. We will perform a sensitivity analyses with adjustment for the use of prostin and milrinone, to account for the effects of these vasodilators on PH.

The following analyses will be performed for the secondary outcomes. The distribution of VIS score in all study participants will be compared between t=0 and t=12 hours after initiation of drug administration using a Wilcoxon signed rank test. The distribution of changes in OI and VIS score from t=0 to t=12 and t=24 hours will be compared between the randomisation groups with a Mann-Whitney test. The overall mortality in the first year of life will be compared between the randomisation groups with Kaplan-Meier curves and the log-rank test. The number of treatment failures, the need for ECMO (in ECMO centres) and the need for medication for PH or chronic lung disease at discharge, and during the first year of life, will be compared between randomisation groups with χ^2^ tests. The number of study drug free days at day 14, the number of ventilation-free days until day 28, the fraction of days with need for medical treatment (excluding the study drug) for PH during the hospital admission and the severity of chronic lung disease using the Bancalari definition will be compared between randomisation groups using Mann-Whitney tests. Deaths will be counted as the worst outcome in these analyses, in accordance with the intention-to-treat principle. The presence of PH at 28 days/discharge, 6 and 12 months according to the echocardiographic parameters will be compared between randomisation groups with a χ^2^ test.

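### The rule that counts deaths as the worst outcome stops short of the PH comparisons at 28 days/discharge, 6 and 12 months, which by default become survivor-only comparisons

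*Protocol article*

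**What the plan says.** All the secondary comparisons stand in one paragraph of the protocol article, section Data analysis. The order matters:

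1. OI and VIS are compared as changes from baseline: "The distribution of changes in OI and VIS score from t=0 to t=12 and t=24 hours will be compared between the randomisation groups", by Mann-Whitney test.
2. One-year mortality is compared by log-rank test.
3. A χ² list follows: treatment failure, ECMO, and "the need for medication for PH or chronic lung disease at discharge" and during the first year.
4. A second Mann-Whitney list follows: "The number of study drug free days at day 14, the number of ventilation-free days until day 28, the fraction of days with need" for PH treatment other than the study drug, and severity of chronic lung disease.
5. Then comes the death rule: "Deaths will be counted as the worst outcome in these analyses, in accordance with the intention-to-treat principle".
6. Last comes later PH: "The presence of PH at 28 days/discharge, 6 and 12 months according to the echocardiographic parameters will be compared between randomisation groups", by χ² test.

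The same section analyses infants as randomised. It provides multiple imputation only for missing independent variables. On ECMO after treatment failure, the section Randomisation, intervention and blinding says "An ECMO procedure may then be started in centres where ECMO is available" and keeps all patients in the intention-to-treat analysis.

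**The concern.** The authors see that death must count in an intention-to-treat comparison of secondary outcomes, and they say so. The sentence that says it refers back to analyses already named, and later PH is named afterwards. PH at those visits is read from an echocardiogram, which cannot exist for an infant who has died. Without a rule, the χ² table holds survivors only.

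This matters because the article itself treats a survival effect as possible. It reports lower mortality with intravenous sildenafil in newborns with PH but without CDH, tests one-year mortality between arms, and has the data safety monitoring board watch for a mortality difference. If one arm keeps alive infants who would have died on the other, those infants are probably sicker and more likely to have PH. They then count against the arm that saved them. The article lists 12-month follow-up of PH among its strengths, so readers will look at this result.

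Two neighbouring outcomes are less clear. An infant who dies in hospital never reaches discharge, and could be coded as missing or, favourably, as needing no medication. An infant placed on ECMO before 12 or 24 hours is among the sickest, and nothing says how OI is then scored.

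**Working it through.** **The plan's own figures.** The article gives no number for this point. The sample size, which is not in dispute here, reproduces. For 64% vs 48%, two-sided 5% and 80% power, with pooled variance under the null:

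n = [1.960·√(2·0.56·0.44) + 0.842·√(0.64·0.36 + 0.48·0.52)]² / 0.16² = 150 per arm.

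The enrolment target of 330 gives 165 per arm, used below.

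**Inputs for the illustration**
- Mortality on iNO, m₁ = 0.27. This is the Introduction's figure for CDH in general, used as a stand-in; the article gives no iNO-arm mortality.
- Mortality on sildenafil, m₂ = 0.20 (assumed).
- PH risk in infants who survive on either drug, a = 0.20 (assumed equal in both arms).
- PH risk in infants who survive only on sildenafil, b = 0.60 (assumed).

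**PH among survivors**
- iNO: a = 0.146/0.73 = 20.0%
- Sildenafil: [a(1−m₁) + b(m₁−m₂)]/(1−m₂) = (0.146 + 0.042)/0.80 = 23.5%
- Difference: 3.5 points against sildenafil

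**Death or PH**
- iNO: 0.27 + 0.146 = 41.6%
- Sildenafil: 0.20 + 0.188 = 38.8%
- Difference: 2.8 points in favour of sildenafil

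**Why the direction reverses.** The survivor-only difference equals (m₁−m₂)(b−a)/(1−m₂), which goes against the life-saving arm whenever b > a. The death-or-PH difference equals (m₁−m₂)(1−b), which favours that arm whenever b < 1.

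**Range.** With m₁ fixed at 27%, sildenafil mortality 17–22%, a = 10–30% and b = 50–80%, the survivor-only difference is 1.3 to 8.4 points against sildenafil. The death-or-PH difference is 1.0 to 5.0 points in its favour.

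**Sampling error in the illustration**
- Survivors: 165·0.73 ≈ 120 and 165·0.80 = 132. SE = √(0.20·0.80/120 + 0.235·0.765/132) ≈ 5.2 points, against a difference of 3.5.
- Death or PH: SE = √(0.416·0.584/165 + 0.388·0.612/165) ≈ 5.4 points, against a difference of 2.8.

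Both differences are smaller than one standard error.

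**Baseline adjustment of OI and VIS (a separate matter).** With equal variances σ² and correlation ρ between baseline and follow-up, a change score has variance 2σ²(1−ρ) and linear ANCOVA has σ²(1−ρ²). The ratio is (1+ρ)/2, or 0.65, 0.75 and 0.85 at assumed ρ of 0.3, 0.5 and 0.7. The variance falls by 35%, 25% and 15%. For rank methods these figures are only approximate.

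**The case against.** The strongest reply is that the article never restricts later PH to survivors. It says infants are analysed as randomised and that all patients' data are used, and a full protocol or analysis plan may settle how deaths are coded. It is true that a survivor-only analysis is the default consequence of the wording and not the wording itself. What remains is that the article does state a death rule, ties it to intention to treat, and places it so that later PH falls outside.

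A reader might also infer more than the documents support:
- *That infants on ECMO drop out of the later PH comparisons.* Nothing removes them, and ECMO does not prevent an echocardiogram at those visits. The ECMO gap concerns OI at 12 and 24 hours only.
- *That deaths are certainly left out of OI change and discharge medication.* Both are named before the rule, so its reference to the analyses may include them. Deaths by 24 hours are also likely to be few, though no figure is given.
- *That 27% is the iNO-arm mortality.* It is the general CDH figure.
- *That a trial conclusion would be overturned.* The illustrated differences are within chance. The primary outcome already includes death to day 28, and mortality has its own test.

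Finally, chronic PH in survivors is a legitimate clinical question, and death or PH overlaps with mortality: in the illustration deaths make up 27 of the 41.6 points on iNO (65%). Both points stand. They are reasons to keep the survivor figure as description, but they do not make it a randomised comparison.

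**Conclusion.** The point holds for PH at 28 days/discharge, 6 and 12 months. As written, this comparison lies outside the plan's own death rule, defaults to survivors, and does not fit the intention-to-treat reason given for that rule. If treatment changes survival, the result can point the wrong way: 20.0% vs 23.5% among survivors, against 41.6% vs 38.8% for death or PH. This rests on the assumed rates, above all that infants saved by treatment have more PH than the rest. It shows a direction, not an expected size.

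For medication at discharge and OI change, the fault is unclear scope. For OI after ECMO starts within 12 to 24 hours, no rule is given. The consequence is limited, because these are secondary outcomes and mortality is reported beside them. The correction is worth making because it is cheap and 12-month PH will be read as a main long-term result. Baseline adjustment and stratification by centre are precision gains and not corrections of an error.

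**What to change.** - **Later PH.** Extend the death rule to 28 days/discharge, 6 and 12 months. Make death or PH the main comparison, and report PH among survivors as descriptive.
- **Medication at discharge.** State that the rule applies, so that an in-hospital death cannot count as needing no medication.
- **OI change.** State that the rule applies, and give the worst rank to infants who die or start ECMO before the 12- or 24-hour measurement.
- **Precision, separately.** Compare OI and VIS at 12 and 24 hours adjusted for the baseline value, for example by rank ANCOVA; Table 1 already schedules the baseline measurement. Stratify the secondary tests by centre, the randomisation factor: Mantel-Haenszel for binary outcomes, stratified log-rank for mortality, van Elteren for rank tests.

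The cost is a few sentences in the analysis plan and slight analysis work, with no new data. The price in interpretation is that death or PH partly repeats the mortality analysis, so its two components should be shown alongside it.

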### Objectives

The primary objective of the study is to determine whether the incidence of PH is lower in CDH patients treated with intravenous sildenafil than in patients treated with iNO, with the primary outcome defined as the absence of PH on echocardiography on day 14 without pulmonary vasodilator therapy and without treatment failure and/or death within the first 28 days after birth. PH is defined as systolic pulmonary arterial pressure >2/3 systolic systemic pressure and/or right ventricular (RV) dilatation/septal displacement and RV dysfunction +/−left ventricular dysfunction.

The secondary outcomes are:

Change in OI after 12 and 24 hours of therapy.Overall mortality.The incidence of treatment failure which is defined as:inability to maintain preductal saturations above 85% (±7 kPa or 52 mm Hg) or postductal saturations above 70% (±5.3 kPa or 40 mm Hg).and/or increase in CO_2_ >70 mm Hg (9.3 kPa) despite optimisation of ventilator management.and/or inadequate oxygen delivery with metabolic acidosis defined as lactate ≥5 mmol/L and pH <7.15 and/or hypotension resistant to fluid therapy and adequate inotropic support resulting in a urine output <0.5 mL/kg/hour.and/or lactate ≥5 mmol/L and pH <7.15.and/or OI consistently ≥40.Time on intervention drug, defined as intervention drug free days after initiation of the intervention, calculated on day 14.Need for ECMO.Ventilator free days on day 28.The use of drugs for PH treatment during the hospital admission.The use of pulmonary and/or cardiac medication at discharge and its total duration of administration.Short-term and long-term PH on echocardiography at 24 hours, 28 days/discharge and 6 and 12 months.The incidence of chronic lung disease.The development of neurological abnormalities evaluated with ultrasound of the brain before the start of the trial, after surgery and before discharge.The external validation of the sildenafil pharmacokinetic - pharmacodynamic (PKPD) model for the pharmacokinetics and the pharmacodynamic effects of sildenafil.

Safety outcomes include adverse events due to the study drugs and the vasoactive-inotropic support (VIS) score.

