#### ​Follow up

After day 14, additional clinical data, such as time on ventilator support (days) and the use of drugs for the treatment of PH, are collected to answer the secondary outcome questions. Also, echocardiographic measurements are taken at 6 and 12 months to evaluate the presence of chronic PH (table 1).

**Table 1 T1:** Procedures and measurements

	Day 0–7 before start therapy	3 hours after start sildenafil	12 hours after start	8 am after start	24 hours after start	Day of surgery, preoperatively	Day after surgery	Day of ECMO, pre- cannulation	8 am after start ECMO	Day 14	Day 28/before discharge	Day 56	6 months	12 months
Echocardiography	X				X					X	X		X	X
Calculation OI	X		X		X									
Calculation VIS score	X		X		X									
Blood sample	X			X		X	X	X	X	X				
Tracheal aspirate	X			X		X	X	X	X	X				
Urine sample	X			X		X	X	X	X	X				
Severity of CLD											X	X		
Ultrasound brain	X						X							
Sildenafil plasma level		X		X		X	X		X					

CLD, chronic lung disease; ECMO, extracorporeal membrane oxygenation; OI, oxygenation index; VIS, vasoactive-inotropic support.

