To externally validate the pharmacokinetic model of sildenafil and its active metabolite (in NONMEM) normalised prediction distribution errors and visual predictive check will be used. Furthermore, the model will be used to predict the drug concentrations from the new data set using simulations, in which we expect that the difference will be less than 20%. To assess whether there is a relationship between the concentration of sildenafil, its active metabolite and the clinical effects, such as OI, VIS score and echocardiography measures, a Mann-Whitney or Student’s t-test will be used.

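### Two-group tests are named for relating sildenafil concentration to OI and VIS score, where a regression on the numeric values is needed

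*Protocol article*

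**What the plan says.** The last secondary outcome under Objectives is this: "The external validation of the sildenafil pharmacokinetic - pharmacodynamic (PKPD) model for the pharmacokinetics and the pharmacodynamic effects of sildenafil". The pharmacokinetic paragraph of Data analysis then gives two separate things.

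- For the pharmacokinetic model: "To externally validate the pharmacokinetic model of sildenafil and its active metabolite (in NONMEM) normalised prediction distribution errors and visual predictive check will be used". A comparison of simulated with observed concentrations follows, with an expected difference under 20%.
- For the concentration-effect question, the aim is put as "To assess whether there is a relationship between the concentration of sildenafil, its active metabolite and the clinical effects". The method named is a two-group test: for the "clinical effects, such as OI, VIS score and echocardiography measures, a Mann-Whitney or" Student's t-test.

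The paragraph gives no groups, no cut-point, and no correlation or regression. Table 1 (Follow up) sets the times of the row "Sildenafil plasma level" and of the OI, VIS and echocardiography rows.

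**The concern.** The aim is to find out whether two quantities are associated; the named tests compare one quantity between two groups. Concentration, OI and VIS score are all numeric, and Data analysis elsewhere treats changes in OI and VIS as distributions. Something must therefore be split in two before either test can run.

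The randomised arms cannot supply the groups, because the iNO arm has no sildenafil exposure under the protocol. An analysis plan that followed this sentence would have to choose a cut. A positive result could depend on that choice, a null result could partly reflect the information lost, and neither would say how the effect changes with concentration.

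**Working it through.** There is no planned figure to reproduce: the article states no sample size, power or cut for this analysis. The check is of the method, followed by an illustration of size.

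**1. What the tests do on undivided data.** Taken literally, a test of concentrations against OI values only detects that the two are on different scales. In a simulated set of 100 infants (assumed concentration mean 200, SD 60; OI mean 15, SD 6), the p-values were:

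| True correlation | Mann-Whitney | t-test |
|---|---|---|
| 0 | 2.6e-34 | 9.3e-87 |
| 0.9 | 2.6e-34 | 1.0e-79 |

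The result is the same with and without a relationship. The tests become meaningful for OI and VIS only after one variable is split.

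**2. Information kept after a split.** Assume a normal exposure and a linear effect. A split that puts a fraction p below the cut c keeps φ(c)² / [p(1−p)] of the information.

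- Median: φ(0) = 0.3989; 0.3989² / 0.25 = 0.637, which is 2/π.
- Upper quartile: φ(0.6745) = 0.3178; 0.3178² / (0.75 × 0.25) = 0.539.

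**3. Power, by simulation.** 4,000 data sets per setting, bivariate normal, one concentration and one effect per infant, two-sided 0.05, median split of concentration for the two-group tests. The correlations and numbers of infants are assumptions. The upper bound of 165 is 330 / 2, with the 330 from Sample size calculation and equal allocation. Fewer are likely, since Laboratory testing says that samples are collected in most, not all, centres and depend on an existing line and/or routine blood tests.

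| Infants | Correlation | Pearson | Spearman | Mann-Whitney | t-test |
|---|---|---|---|---|---|
| 50 | 0.2 | 0.284 | 0.265 | 0.181 | 0.194 |
| 50 | 0.3 | 0.581 | 0.528 | 0.361 | 0.390 |
| 100 | 0.2 | 0.518 | 0.474 | 0.336 | 0.349 |
| 100 | 0.3 | 0.868 | 0.823 | 0.660 | 0.683 |
| 165 | 0.2 | 0.745 | 0.703 | 0.531 | 0.552 |
| 165 | 0.3 | 0.977 | 0.967 | 0.863 | 0.885 |

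**4. Timing in Table 1.**

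| Measurement | Scheduled times |
|---|---|
| Plasma level | 3 h after start of sildenafil; 8 am after start; day of surgery; day after surgery; 8 am after start of ECMO |
| OI, VIS | before start; 12 h; 24 h |
| Echocardiography | before start; 24 h; day 14; day 28/discharge; 6 and 12 months |

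No plasma level shares a column with an OI, VIS or echocardiography measurement. Both levels and effects repeat within an infant, whereas both tests assume independent observations.

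**The case against.** Several objections are fair, and they limit the point.

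- **Echocardiography.** A reader might infer that these tests have no valid use here. That is not so. PH on echocardiography is defined as present or absent, and comparing concentrations between infants with and without PH needs no cut and keeps concentration numeric. It is simple but legitimate, so the criticism covers OI and VIS only.
- **Pharmacodynamic validation.** Because Objectives names both halves of the PKPD model and Data analysis gives checks only for the pharmacokinetic half, a reader might infer that the pharmacodynamic half will go unvalidated. The documents do not support this. The article condenses a fuller protocol that is not shown, and such checks may be set out there or in an analysis plan. Nor does the article offer the two-group tests as model validation; it gives them a separate purpose. The pharmacokinetic checks themselves are suitable.
- **Choice between the two tests.** Naming a parametric test and its rank-based alternative is ordinary protocol wording.
- **Size.** A reader might turn 64% into a claim that 36% of 165 infants are discarded. No infant is excluded, no median split is stated, normality is assumed, and 165 is an upper bound.
- **Timing.** A reader might infer that levels cannot be paired with effects at all. The 8 am sample may fall near 12 h or 24 h, the surgery and ECMO samples can serve the pharmacokinetic validation, and the article does not say that only raw same-time pairs will be used.

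What remains is that, for numeric OI and VIS, the article names a specific method that does not fit the specific question it is given. That is a stated choice, not a detail left to another document.

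**Conclusion.** The point holds for OI and VIS score. The named tests can address their relationship with concentration only after an unstated cut, give no slope, and ignore repeated measures; the sampling times add a pairing problem that the article does not resolve.

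The size is illustrative. About 64% of the information is kept with a median split and about 54% with an upper-quartile split, both assuming a normal exposure and a linear effect. Across the simulated settings, power drops by roughly 0.1 to 0.2. The true loss depends on a cut and a number of sampled infants that the documents do not give.

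This affects one part of one secondary outcome. The primary analysis, the sample size and the other comparisons between randomised arms are not touched.

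**What to change.** For OI and VIS, replace the two-group tests with a regression of the 12 h and 24 h values on continuous sildenafil or metabolite concentration (or exposure), adjusted for the baseline value, with a random effect per infant where measures repeat. Use observed concentrations, or those predicted at 12 h and 24 h by the NONMEM model once its external validation is acceptable, and say which. For echocardiographic PH as a yes/no finding, the two-group comparison of concentrations may stay, or logistic regression on concentration may be used.

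The cost is a change of wording and modest extra modelling with software already planned; no extra samples are needed. The downside is that predicted concentrations come from a model that these same data are meant to test. Their use should therefore depend on the validation result, with a regression on observed levels as the alternative.
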